### Procedure for unblinding if needed {17b}

If a girl/family wishes to withdraw from the trial or if an adverse event leads to withdrawal from the study, then the family will be invited to an end-of-study visit which will be followed by disclosure of treatment allocation. The girl will continue to receive standard care.

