### Criteria for discontinuing or modifying allocated interventions {11b}

In all participating girls, safety markers [blood count, circulating levels of alanine transaminase (ALT), aspartate transaminase (AST), gammaglutamyltransferase (GGT), thyroid-stimulating hormone (TSH), urea, creatinine, electrolyte panel, vitamin B12, folic acid] will be assessed at treatment start, after 6 months and 1 year on treatment, and after 1 year off treatment, as well as upon reporting any adverse events. Glucose blood levels <65 mg/dL and a progressive increase of creatinine, urea, transaminase or potassium levels, will be a reason for discontinuing the medication. In addition, the existence of signs and/or symptoms of hypoglycemia, the appearance of a persistent skin rash, abdominal pain, persistent nausea and/or vomiting, headaches, sinusitis, and severe bacterial infections, will be also a reason for discontinuation. In those cases, hepatic and renal function will be periodically monitored until the disappearance of the symptoms or the normalization of the altered parameters.

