### Outcomes {12}

#### Primary outcome

The primary outcome is annualized bone age (BA) advancement over the on-treatment year. A hand and wrist X-ray of the left hand will be obtained at the treatment start and after 1 year on treatment. BA advancement will be measured by an automated/blinded method called BoneXpert (Visiana, Denmark) [1].

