## Data collection and management

### Plans for assessment and collection of outcomes {18a}

#### Collection of outcomes

*Baseline evaluation (time 0):* will include the clinical visit to collect clinical variables: height, weight, BMI, Tanner stage, waist and hip circumference and their ratio (WHR), SBP, DBP, a hand and wrist X-ray (to assess bone age), MRI (to assess abdominal fat partitioning and hepatic fat) and blood sampling in the fasting state (to assess endocrine-metabolic and inflammation variables and safety markers). Dietary habits will be also recorded through a standard questionnaire (Kidmed).

*Evaluation on treatment (time 6 months and 1 year):* a clinical visit with the same parameters collected at baseline, an abdominal MRI, and a blood sample extraction (to assess endocrine-metabolic and inflammatory variables and safety markers) will be performed after 6 months and after 1 year on treatment. Dietary habits, study adherence, acceptability of the tablet, and adverse events will be also recorded. After 1 year of treatment, a hand and wrist X-ray will be performed for bone age assessment.

*Evaluation post-treatment (time 2 years):* will include a clinical visit 1 year after treatment discontinuation, collecting the same parameters as at time 0, 6 months, and 1 year; in addition, an abdominal MRI scan and a blood sampling (to assess endocrine-metabolic and inflammation variables and safety markers) will be performed. Dietary habits, study adherence, acceptability of the tablet, and adverse events will be also recorded. Six months later a phone call will be made to ascertain the presence or absence of menarche.

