#### Assessment of outcomes

*Bone age:* A hand and wrist X-ray of the left hand will be taken at the Radiology Department either at HJT or HSJD, at treatment start and after 1 year on treatment. At each center, bone age will be determined with the same BoneXpert programme [version 3; February 2021 (Visiana, Denmark)] [38]. This method will yield bone ages by Greulich & Pyle (GP) and by Tanner-Whitehouse 2 (TW2). Bone age maturation will be annualized by calculating the ratio between the increase of BA over the increase in CA (ΔBA/ ΔCA) [38].

*Clinical characterization:* Clinical variables will be obtained during the clinical visits with the pediatric endocrinologist at HJT and HSJD. The same investigator at each center will assess the clinical variables at times 0, 6 months, 1 year, and 2 years. Halfway the second post-treatment year, the girls will be contacted by phone to discuss the absence or timing of menarche.

*Blood sampling:* 23 mL of peripheral blood in a fasting state will be drawn in the early morning at each clinical center, at baseline (time 0), after 6 months on treatment, after 1 year on treatment, and 1 year off treatment. Blood samples will be stored (at −80 °C) at the Pediatric Endocrinology lab (IDIBGI) and at the Metabolic Endocrinology lab (IRSJD) until analyses.

*Endocrine-metabolic variables analysis:*

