### Methods in analysis to handle protocol non-adherence and any statistical methods to handle missing data {20c}

An intention-to-treat analysis will be performed including all participants randomized to either placebo or mini-spiomet, ignoring non-compliance, protocol deviations, withdrawal, and anything that happened after randomization. If necessary, for the withdrawn participants, the missing data will be filled with the data of previous visits.

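### No text shown secures the month-12 bone-age film once a girl stops tablets or is withdrawn, and the carry-forward fallback then gives her zero or undefined bone-age advance

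*Protocol article*

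**What the plan says.** All references are to the protocol article.

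- **Analysis population** (Methods in analysis to handle protocol non-adherence, item 20c): all randomised girls are analysed, "ignoring non-compliance, protocol deviations, withdrawal, and anything that happened after randomization". The same section adds that, if necessary, missing values of withdrawn participants are taken from their previous visits.
- **Primary film** (Primary outcome): "A hand and wrist X-ray of the left hand will be obtained at the treatment start and after 1 year on treatment". Collection of outcomes agrees: "After 1 year of treatment, a hand and wrist X-ray will be performed for bone age assessment". No film is listed at 6 months.
- **Endpoint** (Assessment of outcomes): "the ratio between the increase of BA over the increase in CA".
- **Post-treatment visit** (Collection of outcomes): labelled 2 years, but described as one year after treatment ends.
- **Stopping medication** (Criteria for discontinuing or modifying allocated interventions, item 11b): after the list of reasons for stopping, the follow-up stated is that "hepatic and renal function will be periodically monitored until the disappearance of the symptoms or the normalization of the altered parameters". Bone age is not mentioned.
- **Leaving the study** (Procedure for unblinding if needed, item 17b): for a girl who withdraws, or whose adverse event leads to withdrawal, "the family will be invited to an end-of-study visit which will be followed by disclosure of treatment allocation". She then receives standard care. The content of that visit is not given.
- **Dropout** (Sample size): 21 girls per arm, raised to 32 to allow for up to one third dropping out.

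**The concern.** An intention-to-treat analysis needs the outcome to be sought in every randomised girl at a time counted from randomisation. Here the film is counted from exposure. Read literally, a girl who stops at month 3 never reaches a point that is one year on treatment, and for her a visit one year after stopping falls at month 15, not month 24.

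The fallback makes the gap serious. For most variables, a previous visit supplies a plausible if dated value. For bone age, the only previous value is the baseline one, so carrying it forward asserts that the skeleton did not mature at all. Slower maturation is the benefit the trial hopes to show, so each filled girl counts as an extreme success. Unequal numbers of filled girls would bias the comparison towards the arm with more of them. Equal numbers would swamp the true effect with artificial spread.

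**Working it through.** **1. The plan's own figure.** Inputs from Sample size: means 1.20 and 1.00, SD 0.20, power 90%. The significance level is printed as 0.05%. That value would need 46 per arm, so 5% two-sided is taken as intended.

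n per arm = 2 × (1.960 + 1.282)² × (0.20/0.20)² = 21.01, against 21 stated. With one third lost, 21 / (1 − 1/3) = 31.5, so 32. Both figures reproduce. By t test, power is 88.5% with 21 per arm and 97.6% with all 32.

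**2. What the fallback gives.** Filled bone age at month 12 = baseline bone age, so ΔBA = 0.
- If ΔCA is 1 year, the ratio is 0/1 = 0.
- If age is carried forward as well, the ratio is 0/0. It is undefined, and the girl drops out of an analysis meant to include her.

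**3. Effect of a ratio of 0.** Let k_P and k_A be the filled girls among 32 per arm, with true means μ_P and μ_A.

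Expected difference = μ_A(32 − k_A)/32 − μ_P(32 − k_P)/32.

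The spread also grows. With a share q filled, variance = (1 − q) × 0.04 + q(1 − q)μ². For q = 3/32 and μ = 1.20 this is 0.0363 + 0.1223 = 0.1586, an SD of 0.40, twice the planning value.

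The counts below are assumptions. Rates come from 40,000 simulated trials per row, by unadjusted two-sample t test at two-sided 5%.

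| Filled (placebo, active) | True means | Expected difference | Result |
|---|---|---|---|
| 0, 0 | 1.20, 1.00 | −0.20 | power 97.7% |
| 2, 2 | 1.20, 1.00 | −0.20 × 30/32 = −0.188 | power 67% |
| 3, 3 | 1.20, 1.00 | −0.20 × 29/32 = −0.181 | power 44% |
| 5, 5 | 1.20, 1.00 | −0.20 × 27/32 = −0.169 | power 12% |
| 11, 11 | 1.20, 1.00 | −0.20 × 21/32 = −0.131 | power about 0% |
| 0, 3 | 1.20, 1.20 | −1.20 × 3/32 = −0.113 | 18% false positives favouring active |
| 0, 5 | 1.20, 1.20 | −1.20 × 5/32 = −0.188 | 54% |
| 3, 8 | 1.20, 1.20 | −1.20 × 5/32 = −0.188 | 12% |
| 2, 5 | 1.20, 1.20 | −1.20 × 3/32 = −0.113 | 2% |
| 3, 6 | 1.20, 1.20 | −1.20 × 3/32 = −0.113 | 0.7% |

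The nominal rate in that direction is 2.5%. The last two rows do not exceed it, because the inflated spread masks the bias in the test. The estimate is still wrong by −0.11, more than half the planned effect of 0.20. If more placebo girls were filled, the bias would run the other way.

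**4. Cost of keeping girls who stop.** Take the extreme in which 11 of 32 active girls stop, all films are taken, and the mixture is allowed to widen the SD.
- Stoppers keep half the effect: difference 0.20 × (1 − 0.5 × 11/32) = 0.166, power about 90%.
- Stoppers keep none: 0.20 × 21/32 = 0.131, power about 70%.
- Only 3 stop and keep none: 0.20 × 29/32 = 0.181, power about 94%.

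**The case against.** Much can be said for the protocol.

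- It does distinguish stopping medication (item 11b) from leaving the study (item 17b), and no sentence says that stopping tablets ends participation. The liver and kidney monitoring is an added safety measure that cancels no scheduled visit. Trial design has all girls followed after the treatment year, and there is contact every three months to limit loss.
- Time on treatment may be only a visit label: the abstract defines the outcome over 0–1 year, and other sections use times 0, 6 months, 1 year and 2 years.
- The exit visit might include a film, and an annualised ratio could be computed from it.
- The schedule figure is not shown, and a full protocol exists.

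These points stand against a stronger reading. A reader might infer that girls who stop have no primary outcome at all, or that the trial treats stopping tablets as leaving. The documents do not support either; both are inferences from silence. A reader might also infer that losses fall mainly on the active arm and leave nearly all placebo girls. No source supports that: the background expects gastrointestinal effects of metformin in about 10%, says they usually resolve, and gives no stopping rate, while the one-third allowance is not split by arm.

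They do not remove the point made here. The article itself fixes the film's timing, the exit route, the analysis population and the fallback, and these do not fit together. A film at an early exit would cover a different and shorter period than the stated year. An analysis plan cannot supply a film that was not taken.

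**Conclusion.** The point holds in this form: no text shown secures the month-12 film after a girl stops tablets or is withdrawn, and for withdrawn girls the stated fallback yields a zero or undefined primary outcome. Followed as written, that is a wrong value and not merely an imprecise one.

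The size depends on how many girls are filled and in which arm, and the documents give neither. Over the assumed range, 2 to 5 filled girls per arm reduce power to between 67% and 12%. With no true effect, an excess of 3 to 5 on active shifts the estimate by −0.11 to −0.19, with false positives favouring active from below nominal to 54%. These figures assume the plan's means and SD, a filled ratio of exactly 0 and an unadjusted t test. They do not predict what will happen in this trial. The fallback applies to withdrawn participants and only if necessary, so a girl who stops tablets but attends at month 12 would not be affected.

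**What to change.** 1. In Primary outcome, Collection of outcomes and Assessment of outcomes, define the film and visits as months 6, 12 and 24 after randomisation, whether or not tablets are still taken.
2. In items 11b and 17b, state that stopping tablets does not end study follow-up. Girls who stop, including for an adverse event, are asked to return for the month-12 X-ray, MRI and bloods unless consent to data collection is withdrawn.
3. In item 20c, exclude the primary endpoint from filling with previous-visit data: baseline bone age is not to be carried forward.

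No stopping rule or dose changes. The cost is an amendment to protocol and consent wording. The month-12 visit and film already belong to the schedule for the trial's girls, though the article gives no budget. The statistical downside is a somewhat diluted effect estimate: in the extreme case worked above, power is about 70% to 90%, against 88.5% with only 21 films per arm. That dilution is part of the effect an intention-to-treat analysis is meant to estimate.

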## Data collection and management

### Plans for assessment and collection of outcomes {18a}

#### Collection of outcomes

*Baseline evaluation (time 0):* will include the clinical visit to collect clinical variables: height, weight, BMI, Tanner stage, waist and hip circumference and their ratio (WHR), SBP, DBP, a hand and wrist X-ray (to assess bone age), MRI (to assess abdominal fat partitioning and hepatic fat) and blood sampling in the fasting state (to assess endocrine-metabolic and inflammation variables and safety markers). Dietary habits will be also recorded through a standard questionnaire (Kidmed).

*Evaluation on treatment (time 6 months and 1 year):* a clinical visit with the same parameters collected at baseline, an abdominal MRI, and a blood sample extraction (to assess endocrine-metabolic and inflammatory variables and safety markers) will be performed after 6 months and after 1 year on treatment. Dietary habits, study adherence, acceptability of the tablet, and adverse events will be also recorded. After 1 year of treatment, a hand and wrist X-ray will be performed for bone age assessment.

*Evaluation post-treatment (time 2 years):* will include a clinical visit 1 year after treatment discontinuation, collecting the same parameters as at time 0, 6 months, and 1 year; in addition, an abdominal MRI scan and a blood sampling (to assess endocrine-metabolic and inflammation variables and safety markers) will be performed. Dietary habits, study adherence, acceptability of the tablet, and adverse events will be also recorded. Six months later a phone call will be made to ascertain the presence or absence of menarche.

#### Assessment of outcomes

*Bone age:* A hand and wrist X-ray of the left hand will be taken at the Radiology Department either at HJT or HSJD, at treatment start and after 1 year on treatment. At each center, bone age will be determined with the same BoneXpert programme [version 3; February 2021 (Visiana, Denmark)] [38]. This method will yield bone ages by Greulich & Pyle (GP) and by Tanner-Whitehouse 2 (TW2). Bone age maturation will be annualized by calculating the ratio between the increase of BA over the increase in CA (ΔBA/ ΔCA) [38].

*Clinical characterization:* Clinical variables will be obtained during the clinical visits with the pediatric endocrinologist at HJT and HSJD. The same investigator at each center will assess the clinical variables at times 0, 6 months, 1 year, and 2 years. Halfway the second post-treatment year, the girls will be contacted by phone to discuss the absence or timing of menarche.

*Blood sampling:* 23 mL of peripheral blood in a fasting state will be drawn in the early morning at each clinical center, at baseline (time 0), after 6 months on treatment, after 1 year on treatment, and 1 year off treatment. Blood samples will be stored (at −80 °C) at the Pediatric Endocrinology lab (IDIBGI) and at the Metabolic Endocrinology lab (IRSJD) until analyses.

*Endocrine-metabolic variables analysis:*
The clinical laboratory at both HJT and HSJD will be responsible for analyzing (1) glucose (by the glucose oxidase method); (2) fasting insulin, IGF-I, SHBG, and usCRP (by immuno-chemiluminescence); (3) LH, FSH, and oestradiol (by immuno-chemiluminescence); (4) total cholesterol, LDL-cholesterol, HDL-cholesterol, and triglycerides (by molecular absorption spectrometry).Circulating testosterone and androstenedione concentrations will be centrally assessed at the Bioanalysis Research lab [Institut Hospital del Mar d'Investigacions Mèdiques (IMIM), Hospital del Mar] by liquid chromatography-tandem mass spectrometry. The free androgen index (FAI) will be calculated with the following formula: testosterone (nmol/L) × 100/SHBG (nmol/L).The analysis of circulating HMW-adip, GDF-15, and CXCL14 concentrations will be centralized at the Metabolic Endocrinology laboratory (IRSJD). Circulating levels of HMW-adip will be analyzed by ELISA (Millipore, St Louis, MO), with intra- and inter-assay coefficients of variation (CVs) <9%. Serum GDF-15 will be assessed using a specific human ELISA kit (R&D Systems, Minneapolis) with intra- and inter-assay CVs <6%. Serum CXCL14 will be assessed using a specific ELISA kit (Ray Biotech, Norcross, GA, USA), with a sensitivity of 0.7 ng/ ml, and inter- and intra- assay CV less than 12%.

*Safety markers analysis:* The clinical laboratories at HJT and HSJD will analyze (1) blood count (by flow cytometry and colorimetric assay); (2) circulating levels of ALT, AST, GGT, TSH, urea, electrolyte panel, and creatinine (by molecular absorption spectrometry); and (3) vitamin B12 and folic acid (by immuno-chemiluminescence).

*Abdominal and hepatic fat assessment:* Abdominal fat distribution *(subcutaneous and visceral)* and intrahepatic fat will be analyzed by MRI at both clinical sites with the same scan [multiple slice 1.5 Tesla scan (Signa LX Echo Speed Plus Excite, General Electric Healthcare, Milwaukee, WI)]. The assessments will be performed at Clínica Girona (Girona) and CETIR Medical Centre (Barcelona). Scans will be performed by the same operator at each center, blinded to the treatment allocation, at times 0, 6 months, 1 year, and 2 years. A central reader blinded to treatment allocation will be appointed to process and interpret the images from both study centers (QUIBIM, Valencia, Spain).

*Dietary habits:* The quality of the dietary habits will be assessed by a modified version of the Kidmed questionnaire. Girls will complete the test during the clinical visits at the corresponding center (at times 0, 6 months, 1 year and 2 years).

*Acceptability of the tablet:* The patient's opinion regarding the palatability and swallowability of the tablet will be recorded by using a simple questionnaire with numerical rating scales and the integrated 100 mm visual analog scale (VAS)/facial hedonic scale [3, 4]. Patients will answer the questionnaire during the clinical visits at each center at times 6 months and 1 year.

All outcomes will be measured as previously described (domain, specific measure, and time points), stated as mean values, and compared between groups at the specific time points.

Figure 2 depicts the schedule of enrolment, interventions, and assessments.

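### Locally assayed markers: with two hospital laboratories and no centre term stated, single-time-point comparisons can lose some power and pooled correlations can be spurious (minor, secondary outcomes only)

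*Protocol article*

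**What the plan says.** All of the following is in the protocol article.

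- **Local assays** (Assessment of outcomes {18a}): "The clinical laboratory at both HJT and HSJD will be responsible for analyzing" glucose, then "fasting insulin, IGF-I, SHBG, and usCRP (by immuno-chemiluminescence"), then "LH, FSH, and oestradiol (by immuno-chemiluminescence"), then the lipids. One detection method is named per analyte for both hospitals. No common platform or cross-calibration is mentioned.
- **Central assays** (same section): "Circulating testosterone and androstenedione concentrations will be centrally assessed at the Bioanalysis Research lab", and "The analysis of circulating HMW-adip, GDF-15, and CXCL14 concentrations will be centralized at the Metabolic Endocrinology laboratory (IRSJD"). That makes five centralised markers.
- **Derived indices**: FAI is "testosterone (nmol/L) × 100/SHBG (nmol/L"), a central numerator over a local denominator. HOMA-IR rests on glucose and insulin, both local.
- **Comparison** (end of the same section): outcomes are "stated as mean values, and compared between groups at the specific time points".
- **Analysis** (Statistical methods {20a}): repeated-measures ANOVA in models adjusted for potential confounders that are not listed, plus correlation and multiple regression among bone age, clinical, endocrine-metabolic and imaging variables.
- **Randomisation** (Sequence generation {16a}): one list per centre, 32 girls each, 16 per arm.

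**The concern.** If each girl's samples go to her own hospital's laboratory, which is implied but not stated, laboratory and centre are the same factor. A calibration difference then becomes a fixed shift between two halves of the trial. An analysis that pools the values without a centre term counts that shift as random variation between girls.

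Two uses of the data are exposed. One is the comparison of group means at a single visit. The other is the set of correlations and regressions meant to link endocrine-metabolic changes with fat and bone maturation. The balance of arms within centre does not protect the second, because two markers shifted by the same laboratory move together whatever the treatment.

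**Working it through.** **Inputs.** From the document: 64 girls, two centres of 32, 16 per arm in each. The document gives no laboratory difference and no power figure for these markers. Its sample size of 21 per arm concerns bone age and reproduces at a two-sided 5% level: 2 × [0.2 × (1.960 + 1.282) / 0.2]² = 21.0. It has no bearing here. Assumption: an additive offset of d within-laboratory SDs, with d from 0.5 to 1.

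**1. Bias between arms.** With 16:16 in each centre, the offset enters both arm means equally (d/2 each) and cancels from their difference. The bias is zero.

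**2. Comparison at one visit without a centre term.** The true sampling variance of the arm difference is unchanged. The estimated variance is inflated by the factor 1 + d²/4, so the test statistic shrinks by the square root of that factor. For an effect otherwise detected with 80% power (standardised 1.960 + 0.842 = 2.802):

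| d | 1 + d²/4 | SE factor | Power = Φ(2.802 − 1.960 × SE factor) | False-positive rate = 2[1 − Φ(1.960 × SE factor)] |
|---|---|---|---|---|
| 0 | 1.000 | 1.000 | 80.0% | 5.0% |
| 0.5 | 1.0625 | 1.031 | 78.3% | 4.3% |
| 1.0 | 1.250 | 1.118 | 72.9% | 2.8% |

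A simulation of the actual layout (4,000 runs, effect 0.7 SD) agrees. Power was 79.3%, 77.6% and 70.3% for d = 0, 0.5 and 1, and the false-positive rate was 4.8%, 4.6% and 3.3%. With a centre term, power was 79.4%, 79.2% and 77.6%, and the false-positive rate was about 5% throughout.

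**3. Treatment-by-time contrast.** A stable additive offset subtracts out of each girl's change. In the same simulation (assumed within-girl correlation 0.6, mean 10, SD 3), power for change was 87.5% at d = 0 and 87.1% at d = 1. A proportional difference of 20% does not cancel exactly on the raw scale, but it lowered power for change only from 87.5% to 86.4%. At a single visit it lowered power from 79.3% to 75.4%.

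**4. Pooled correlations.** Take two locally assayed markers that are unrelated within each centre, both shifted by d in the same direction. The between-centre covariance is d²/4 and each variance is 1 + d²/4, so r = (d²/4) / (1 + d²/4).

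- d = 0.5: 0.0625 / 1.0625 = 0.06; p < 0.05 in about 7% of simulated trials of 64 girls.
- d = 1: 0.25 / 1.25 = 0.20; p < 0.05 in about 37%.

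Shifts in opposite directions give the same size with a negative sign. If only one of the two variables is shifted, for example a local hormone against BoneXpert bone age, nothing spurious arises. A real correlation is then reduced by the factor 1/√(1 + d²/4), which is 0.97 and 0.89 for d = 0.5 and 1.

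**5. Why the log scale.** A laboratory ratio k becomes the constant ln k after taking logs, and a centre term removes a constant. This carries over to the indices. ln FAI = ln testosterone + ln 100 − ln SHBG, so an SHBG ratio k shifts it by −ln k. For HOMA-IR, a product of glucose and insulin, the two shifts add.

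**The case against.** The strongest objection is that the governing analysis is the adjusted repeated-measures ANOVA in Statistical methods {20a}, not the sentence on means in the data-collection section. Under that ANOVA a stable offset drops out of the treatment-by-time contrast. This stands. A reader might infer that the results are simply pooled as raw means, or that any laboratory difference degrades every endocrine-metabolic result. The documents do not support either reading.

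Three more points stand in whole or part:

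- No laboratory difference is documented, and one method per analyte is named for both hospitals. The offsets used here are assumptions.
- Platforms, cross-calibration and the covariate list are details that an article may leave to the full protocol, a laboratory manual or the analysis plan. Their absence is not counted as a fault. What is stated is a choice: local assay for some markers and central assay for others, with visit-by-visit comparisons and correlations across the whole sample.
- Central assay is a debatable trade-off. The article says "Blood samples will be stored (at −80 °C) at the Pediatric Endocrinology lab (IDIBGI) and at the Metabolic Endocrinology lab (IRSJD) until analyses", but not that spare aliquots exist for further assays. Centralising the hormones alone, without glucose, would leave HOMA-IR partly local.

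The objection does not cover the comparisons at individual visits or the correlation analyses. Adjustment for potential confounders does not clearly bring centre in either, since centre is balanced between arms by design and so would not naturally be listed as a confounder.

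**Conclusion.** The point holds in a limited form and is minor. Neither arm is favoured, false positives in the treatment comparisons fall rather than rise, and the bone-age primary outcome is untouched. What remains concerns secondary outcomes only:

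- **Single-visit comparisons without a centre term** are conservative. Power falls from about 80% to about 78% at an assumed offset of 0.5 SD, and to about 71% to 73% at 1 SD.
- **Pooled correlations between two locally assayed markers** can show r of about 0.06 to 0.20, or the same with a negative sign, where no relation exists.

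These sizes rest on the assumed offsets, on each girl being assayed at her own hospital throughout, and on no centre term being used. If the laboratories agree closely, the effect is negligible. If the analysis already includes centre, little remains beyond differences that drift over the study.

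**What to change.** In Statistical methods {20a}, and in the closing statement of Assessment of outcomes {18a} on comparing means, state that glucose, insulin, IGF-I, SHBG, usCRP, LH, FSH, oestradiol, lipids, FAI and HOMA-IR are analysed on the log scale with centre (equal to laboratory, and already a randomisation stratum) as a fixed term. Apply this to the between-group comparisons and to the correlation and regression analyses, where it amounts to within-centre (partial) correlations. State that each girl's samples are assayed at her own centre throughout, and how values below an assay's limit are handled before taking logs.

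The cost is a few sentences and one degree of freedom per model, with no change for participants. Central assay of stored aliquots is optional. It would need shipment, a batch run and confirmation that enough sample is kept, and it would have to include glucose if HOMA-IR is to come fully from one laboratory.
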